#### District randomization, village selection, and randomization

The Ministry of Health chose the Dosso region of Niger for the RMA intervention. This region has five districts from which three districts, Dosso, Doutchi, and Loga, were selected for participation. Based on the logistical challenges of providing all RMA intervention approaches in each district, each district was randomly assigned to one of the three intervention approaches (home visits alone, small groups alone, or a combination), with controls selected across all three districts. Based on power analyses (described below), the minimum number of clusters in each of the four arms was 12, requiring inclusion of 16 villages across each of the three districts (12 intervention and 4 control). Village selection and randomization followed a multi-stage process whereby eligible villages in the three districts were first identified based on the following criteria: 1) rural (i.e., not designated as a market town or city), 2) Hausa- or Zarma-speaking, 3) a minimum of 1000 inhabitants, and 4) located within 5 km of a *centre de santé intégré* (CSI) or *case de santé* (CS) health facility. There were 101 villages in Dosso, 110 in Doutchi, and 36 in Loga that met these criteria. From the eligible villages, we then stratified villages based on three level of health service provision: 1) villages with CSIs, larger health facilities serving multiple villages where doctors, nurses, and midwives provide the full contraceptive method mix and related counseling; 2) villages with CSs, village-level facilities where community health agents provide a subset of contraceptive methods; and 3) villages with neither CSI nor CS. Among the 247 total eligible villages across the three districts, 21% had a CSI, 56% had a CS, and 23% had neither. In order to select a sample of villages within each district that was representative of the distribution of health facilities across the region, we randomly selected nine villages with a CS, three with a CSI, and four with neither in each of the three districts. To create a control arm representative of villages in each district, and that included representation of all levels of health facility, we randomly assigned four of the total 16 villages per district to the control condition, consisting of two villages with a CS, 1 with a CSI, and 1 with neither. The remaining 12 villages were assigned to the intervention condition assigned to that district (see Fig. 3).

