#### Data analysis

##### Planned analytic approach

A difference-in-difference approach utilizing multi-level, mixed-effects logistic regression models will be used to evaluate associations between intervention exposure and the primary and secondary outcomes identified above. The equivalent linear regression models will also be examined for significant findings in order to more clearly interpret results. These models will take into account the multiple study arms, cluster randomization, and repeated measurements over time. All models will include time (baseline or follow-up), treatment arm, district, and select covariates as fixed effects as well as a time by treatment interaction term. Descriptive analyses to describe the frequency of demographics and behavioral and social constructs as well as bivariate analyses to assess differences in demographics by treatment group and by loss to follow-up will be conducted. Any characteristics identified as significantly associated with treatment or female loss to follow-up at the *p* < 0.20 threshold will be considered as potential covariates (fixed effects) in adjusted models assessing effects of the intervention. Collinearity of covariates will be assessed, and highly collinear covariates may be removed from final models.

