Study analyses will take into account clustering within villages using nested random effects specifications due to repeated measurements over time of individuals nested within villages. Models to assess the role of male engagement will include a three-level predictor of male participation in either household visits or small groups and include only those arms that received that intervention activity. Outcome analyses will use an intent-to-treat approach; per-protocol analyses will be conducted secondarily. Missing data on demographics and birth history will be computed where alternate data is available (e.g. calculating age from date of birth if age is not provided); however, no missing data will be imputed. All scales to be used as outcomes will be assessed for internal reliability at baseline using exploratory factor analysis and Cronbach’s alpha. If scales are multifactorial or not internally reliable, they may be modified to more accurately reflect the intended construct and/or be presented as individual item outcomes. Analyses will be conducted using STATA version 14.2® (StataCorp LLC, 2015) [28] and SAS version 9.4® (SAS Institute Inc., 2018) [29] programming applications. Trial results will be presented to the Ministry of Health of the Republic of Niger then communicated via peer review journals and scholarly meetings as well as meetings with national/international stakeholders.

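### The model fixes district but not the facility level by which controls were allocated, and a p < 0.20 screen on treatment and loss cannot be relied on to bring it in

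*Protocol article*

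**What the plan says.** The Protocol article's section on district randomization and village selection states that "we then stratified villages based on three level of health service provision": villages with a CSI, villages with a CS, and villages with neither. For each district, "we randomly selected nine villages with a CS, three with a CSI, and four with neither in each of the three districts". Controls were then set by level: "we randomly assigned four of the total 16 villages per district to the control condition, consisting of two villages with a CS". The other two controls per district were a CSI village and a village without either facility. The same section explains why the levels differ: a CSI offers all contraceptive methods with counselling, a CS only some of them.

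The Planned analytic approach lists the model terms: "All models will include time (baseline or follow-up), treatment arm, district, and select covariates as fixed effects as well as a time by treatment interaction". The random part covers "clustering within villages using nested random effects specifications due to repeated measurements over time of individuals nested within villages". Facility level appears in neither list.

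The remaining covariates follow a two-step rule. The first step is a bivariate screen: "Any characteristics identified as significantly associated with treatment or female loss to follow-up at the" cut-off of p < 0.20 become candidates for the adjusted models, without being certain of entry. The second step allows that "highly collinear covariates may be removed from final models". The between-group tests that feed the first step are described as tests of demographics. The article also states that no missing data will be imputed.

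**The concern.** Facility level was a stratification factor in the allocation, the chance of being a control differs across its levels, and it governs the supply of the methods that make up the primary outcome. A factor with those properties belongs in the analysis model. District, the other design factor, is there.

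The screen is a poor substitute, for four reasons.

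- It asks whether a variable differs between arms or between women lost and retained, not whether it predicts contraceptive use. It can admit variables of no value and pass over strong predictors.
- Each intervention approach sits in one district. An unadjusted comparison across arms will therefore also flag plain district differences, which the model already handles.
- Loss is known only after follow-up. The covariates of the primary model cannot be known beforehand and may differ between 24 and 40 months.
- Variables that pass are only candidates, and collinear ones may then be dropped. Both steps leave the final choice to judgement made with the data in hand.

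**Working it through.** **1. Village counts (from the randomization section).** Selected per district: 9 + 3 + 4 = 16. Controls: 2 + 1 + 1 = 4. Intervention: 16 − 4 = 12. This reproduces the article's own 12 and 4.

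| Level | Selected | Control | Intervention | Control share | Mix of controls | Mix of intervention |
|---|---|---|---|---|---|---|
| CS | 9 | 2 | 7 | 2/9 = 22.2% | 50.0% | 58.3% |
| CSI | 3 | 1 | 2 | 1/3 = 33.3% | 25.0% | 16.7% |
| Neither | 4 | 1 | 3 | 1/4 = 25.0% | 25.0% | 25.0% |

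The mix is the same in every district, so it also holds for each intervention arm (7/2/3) against the pooled controls (6/3/3).

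**2. Would the screen select facility level?** Pearson chi-square of level by arm, no continuity correction. The article does not state the unit of analysis, so both are shown.

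- Villages as units (48): any intervention against control, chi-square 0.44 on 2 df, p = 0.80. One arm against control, 0.28 on 2 df, p = 0.87. Four arms, 0.44 on 6 df, p = 0.998. Not selected.
- Women as units, clustering ignored, with an assumed 22 to 25 women per village: four arms, p = 0.13 to 0.085. One arm against control, p = 0.048 to 0.031. Selected.

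The entry of a design factor would thus turn on the choice of unit, provided it is tested at all: it is a village attribute, and the tests are described for demographics.

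**3. How often does the screen flag nothing of substance?** With k independent characteristics and no true differences, the chance that at least one passes is 1 − 0.8^k: 67% for k = 5, 89% for k = 10, 96% for k = 15. The number of characteristics is my assumption. The figure shows that the model depends on the data; it does not show bias.

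**4. Size of the facility effect on the estimate.** The difference-in-difference removes any facility difference that is constant over time. Suppose change in CSI villages differs by d from the other two levels, which change alike. Without adjustment, the estimate shifts by (2/12 − 3/12) × d = −0.083d:

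- d = 5 points: 0.4 points
- d = 10 points: 0.8 points
- d = 20 points: 1.7 points

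The shift works against the intervention if use grows faster in CSI villages, and in its favour if it grows more slowly. The values of d are assumptions. The calculation is on the percentage-point scale, whereas the main model is logistic.

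**5. Form of the adjustment.** Take village means of equal variance and use relative variances for one arm against control.

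- No stratification, 12 against 12: 1/12 + 1/12 = 0.167.
- Common facility strata, controls pooled over districts: the weights (intervention × control / total) are 7×6/13 = 3.23, 2×3/5 = 1.20 and 3×3/6 = 1.50. Sum 5.93, variance 1/5.93 = 0.169, about 1% more before any gain from adjustment.
- District-specific facility strata, 12 against the 4 controls of the same district: 7×2/9 = 1.56, 2×1/3 = 0.67, 3×1/4 = 0.75. Sum 2.97, variance 1/2.97 = 0.336, about double.

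A common facility-by-time term is therefore cheap; a district-specific one is not.

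**The case against.** The strongest reply is that little is at stake. The imbalance is whole-number rounding: four controls in proportion to 9/3/4 would be 2.25/0.75/1, and the article uses 2/1/1. The planned contrast already cancels constant facility differences. Variables passing the screen are only candidates, and the term for select covariates does not exclude facility level, so the matter could be settled in an analysis plan that is not shown. Adjusting for predictors of loss is also sound when nothing is imputed, since a likelihood-based mixed model relies on dropout being explained by what is in the model.

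Much of this stands. It limits the size of the problem, and it means that predictors of loss should stay in the model. It does not rescue the rule. The article itself states the model terms and the selection criterion, so this is more than detail left to another document; choosing by between-arm p-value remains a poor criterion, and nothing commits the trial to including the factor.

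A reader might infer a larger harm in two ways. One is that the unequal shares materially bias the trial. The documents give no rates of change by facility level, so any bias figure rests on an assumed d. The other is a sizeable loss of precision. With ICC 0.05, 20 women per village (240/12) and strata assumed to explain 30% of between-village variance, adjustment would cut the variance of a village mean by 0.3 × 0.05 / (0.05 + 0.95/20) = 15%. That applies to a comparison of village means at a single time. The planned effect is the time-by-treatment contrast, where constant village differences largely cancel, so the 15% does not carry over.

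**Conclusion.** The point holds, at modest size. The counts are exact: control shares of 1/3, 2/9 and 1/4, and CSI villages at 25% of controls against 16.7% of intervention villages. The model list names district and omits facility level, and the screen cannot be relied on to supply it.

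The remaining risk has three parts: a shift of about 0.4 to 1.7 percentage points if change in CSI villages differs by an assumed 5 to 20 points from the other levels; some precision, which the documents do not allow me to quantify; and a primary model that is not settled before the data are seen. The first part assumes the planned village mix. One village withdrew after baseline, its arm and level are not stated, and the mix actually analysed may differ slightly. No sample-size figure is affected. The change is worth making because it costs almost nothing.

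**What to change.** In the Planned analytic approach:

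- Name facility level (three levels) and a facility-by-time interaction as fixed effects in all models, next to district. With time as baseline or follow-up this takes 2 + 2 = 4 degrees of freedom. Keep the interaction common to all districts.
- Replace the p < 0.20 screen by a list, fixed in advance, of baseline characteristics expected to predict contraceptive use, for example age and number of living children. Leave out baseline contraceptive use, which is already an outcome observation in the model.
- Keep expected predictors of loss in the models, named in advance rather than chosen by p-value.
- Retain between-arm comparisons of characteristics for description only.

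The cost is analysis wording and a few degrees of freedom among 47 villages. No new data and no change in sample size are needed.

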**Methods:**

Using a four-arm cluster randomized control design, the RMA study seeks to assess whether household visits only (Arm 1), small group discussions only (Arm 2), or a combination of both (Arm 3), as compared to controls (no intervention – Arm 4), improve modern contraceptive method use among married adolescent girls and young women (AGYW), age 13–19 years-old, in three districts of the Dosso region. Intervention conditions were randomly assigned across the three districts, Dosso, Doutchi, and Loga. Within each district, eligible villages were assigned to either that intervention condition or to the control condition (12 intervention and 4 control per district). Across the three intervention conditions, community dialogues regarding modern contraceptive use were also implemented. Data for the study was collected at baseline (April – June 2016), at 24 months post-intervention (April – June 2018), and a final round of data collection will occur at 40 months post-intervention (October – December 2019).

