##### Knowledge of contraceptive methods

This measure is constructed of 14 items covering knowledge of modern contraceptive methods and reproductive health. Items included in this measure were adapted from recommendations by USAID and Intrahealth International, and research by Frost, Lindberg, and Finer [21–23]. Multiple choice questions to be included in this construct include: 1) “How much time should a woman wait between giving birth and becoming pregnant again?” 2) “For the health of the mother and the baby, how much time should a woman wait between a miscarriage (a pregnancy that did not result in a birth) and becoming pregnancy again?” Response options for these two questions included: 1) zero to six months, 2) six months to a year, 3) one to two years, 4) more than two years, 5) you don’t know how much time she should wait. True or false questions adapted from Frost, Lindberg, and Finer [22] include: 1) “Contraceptive pills are effective even if a woman misses taking them for two or three days in a row;” 2) “After a woman stops taking contraceptive pills, it’s possible for her to get pregnant right away;” 3) “An IUD cannot be felt by a woman’s husband during sex;” 4) “An IUD can get permanently stuck in a woman’s body;” 5) “Women using an injectable contraceptive must get an injection every three months;” 6) “Using an injectable contraceptive can cause a woman to never be able to have children again;” 7) “Implants or an IUD can be removed early if a woman wants to get pregnant;” 8) “If a woman wanted to secretly delay having her next child, an IUD or injectable contraceptive could be used without anyone in her family knowing;” 9) “It’s okay to use the same condom more than once;” 10) “LAM is an effective form of delaying pregnancy even after the woman’s menstrual bleeding has returned after giving birth;” 11) “From one menstrual period to the next, are there certain days when a woman is more likely to become pregnant again;” and 12) “After the birth of a child, a woman can become pregnant before her menstrual period has returned.” Each correct response was assigned one point, with the resulting summary score ranging from 0 to 14.

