##### Attitudes towards family planning

This measure consists of two items adapted from Camber Collective’s tool for segmentation of family planning clients in Niger [24] that reflect attitudes towards and acceptability of spacing and limiting births. The items are as follows: 1) “I think it is acceptable for a young wife to wait two years after having her first child to become pregnant again;” and 2) “It is acceptable for a couple to try to limit the number of children they have.” Response options for both questions were agree and disagree with one point assigned to each “agree” response. Based on their responses to these two questions, participants will be assigned a score between 0 and 2 with a higher score representing attitudes more supportive of modern contraceptive method use.

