##### Perceived community norms regarding contraceptive method use

Participants are asked two questions about their perceptions of community acceptance regarding modern contraceptive method use. These items were developed to align with RMA intervention activities. The items are as follows: 1) “Men in your community think that it is acceptable for their wives to use a family planning method to delay or space pregnancies.” and 2) “People in your community think a young wife who uses a family planning method to delay or space pregnancies is not fulfilling her duty to her family.” Response options for both questions were agree and disagree with one point assigned to each “agree” response. Based on their responses, participants will each be assigned a score between 0 and 2 with a higher score representing perceived community norms more supportive of modern contraceptive method use.

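### One reliability rule covers every summed secondary score, but factor analysis cannot assess the two-item scores and low internal consistency is no valid reason to alter the 0–14 knowledge count

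*Protocol article*

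**What the plan says.** The rule stands in the protocol article under Planned analytic approach. Its scope is every scale used as an outcome: "All scales to be used as outcomes will be assessed for internal reliability at baseline using exploratory factor analysis and Cronbach’s alpha". Its consequence follows directly: "If scales are multifactorial or not internally reliable, they may be modified to more accurately reflect the intended construct and/or be presented as individual item" […].

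Four secondary outcomes are summed scores, each with its own definition:

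- **Knowledge of contraceptive methods.** "This measure is constructed of 14 items covering knowledge of modern contraceptive methods and reproductive health". Scoring: "Each correct response was assigned one point, with the resulting summary score ranging from 0 to 14".
- **Attitudes towards family planning.** Two agree/disagree items. "Based on their responses to these two questions, participants will be assigned a score between 0 and 2".
- **Perceived community norms regarding contraceptive method use.** "Participants are asked two questions about their perceptions of community acceptance regarding modern contraceptive method use". Scoring: "Response options for both questions were agree and disagree with one point assigned to each “agree” response".
- **Self-efficacy to use contraception.** Six agree/disagree items, one marked as reverse coded, summed to 0–6.

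Modern contraceptive use (the primary outcome), intimate partner violence and intention to use are yes/no classifications, so the rule does not reach them.

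**The concern.** The outcome sections fix four scores exactly, and the analysis section then makes all four replaceable by a single criterion. That criterion fits a multi-item scale meant to measure one underlying trait, as self-efficacy is. It fits the other three badly.

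For the two-item scores, half of the planned check has no content. For knowledge, the items are separate facts about pills, IUDs, injectables, implants, condoms, lactational amenorrhoea, fertile days and birth spacing. A woman may know one and not another. Low agreement among such items says that the facts are learned separately; it does not say that the number known is a bad outcome. Dropping or splitting items on that ground could remove content that the programme teaches.

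These scores carry the contraceptive part of the first four hypotheses in the Study overview (knowledge, attitudes, norms, self-efficacy). If they are changed, the reported results no longer test the outcomes as defined.

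**Working it through.** The article gives no alpha, cut-off or number of factors, so there is no figure to reproduce. The cut-offs of 0.60 and 0.70, the endorsement rates and the correlations below are assumptions, used to show the range.

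**Item counts.** Knowledge: 2 multiple-choice + 12 true/false = 14, which agrees with the 0–14 range. Attitudes and norms: 2 each. Self-efficacy: 6.

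**Can factor analysis test for one dimension?** The degrees of freedom of a one-factor model with p items are ((p − 1)² − (p + 1))/2.

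- p = 2: (1 − 3)/2 = −1, not identified
- p = 6: (25 − 7)/2 = 9
- p = 14: (169 − 15)/2 = 77

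Software may still print a result for two items, but the eigenvalues of the correlation matrix are 1 + r and 1 − r. Exactly one exceeds 1 whenever r is not zero, so the common eigenvalue rule could never report two factors.

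**What does alpha need?** Standardised alpha = k·r/(1 + (k − 1)·r), with r the mean inter-item correlation. Solved for r: r = α/(k − α(k − 1)).

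| Items | r for α = 0.70 | r for α = 0.60 |
|---|---|---|
| 2 | 0.7/1.3 = 0.54 | 0.6/1.4 = 0.43 |
| 6 | 0.7/2.5 = 0.28 | 0.6/3.0 = 0.20 |
| 14 | 0.7/4.9 = 0.14 | 0.6/6.2 = 0.10 |

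For two items, alpha is 2r/(1 + r), a transform of one correlation: r = 0.2 gives 0.33 and r = 0.3 gives 0.46.

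**Ceiling for two agree/disagree items.** If everyone who agrees with the less popular item also agrees with the other, the covariance is min(p1, p2) − p1·p2. With assumed endorsement of 80% and 40%, it is 0.40 − 0.32 = 0.08, and the item variances sum to 0.16 + 0.24 = 0.40. The largest possible alpha is then 2 × (1 − 0.40/0.56) = 0.57. At 60%/40% the ceiling is 0.80; at 50%/50% it is 1.00. Unequal popularity alone can therefore keep alpha below 0.70.

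**Knowledge.** With an assumed mean r of 0.05 to 0.10, alpha is 0.70/1.65 = 0.42 to 1.40/2.30 = 0.61. At r of about 0.14 it reaches 0.70. Both methods can be run; the question is what a low value should be allowed to trigger.

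**Norms coding.** The second norms item says that a young wife who uses family planning fails in her duty. Agreement earns a point, although a higher score is meant to be more supportive. If the two items correlate at an assumed −0.2, alpha is −0.4/0.8 = −0.50 as coded and 0.4/1.2 = 0.33 with that item reversed.

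**Most that the wording permits.** If all four scores were split, 4 outcomes would become 14 + 2 + 2 + 6 = 24.

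**The case against.** The strongest reply is that the rule is harmless. It uses baseline, pre-intervention data, which carry no information on the treatment contrast at follow-up. It says that scales may be changed, not that they must be, and any change has to serve the intended construct. All of this stands.

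A reader might infer that outcomes will be redefined once follow-up responses have been seen, since the Abstract reports a round "at 24 months post-intervention (April – June 2018), and a final round of data collection will occur at 40 months" while the scale check is still in the future tense. The documents do not support that. The stated input is baseline data, no section says that 24-month responses will inform the choice, and the tense is mixed: the Data collection section still treats the 24-month round as ahead.

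Other points on this side also hold:

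- Alpha can be computed for two items, and their correlation is worth knowing before they are summed.
- Alpha on right/wrong items equals KR-20, a common description of a knowledge test. It is not a wrong statistic for the quiz.
- A reader might infer that three of the four scores are bound to fail. That needs both an assumed cut-off and assumed low correlations; the article reports no baseline item responses.
- The missing cut-off, item-removal rule and lock date are details that an analysis plan may hold, and are not counted here.
- The check could do good by exposing the norms coding.

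What the reply does not meet is the scope. The article itself sends every scale through the same check, including two that factor analysis cannot assess and one for which low consistency is not a defect. An analysis plan that added cut-offs would still inherit that scope.

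**Conclusion.** The point holds in a limited form. Factor analysis cannot do its job for two of the four summed scores (−1 degrees of freedom); this depends on no assumption. Alpha for those two is one correlation restated and needs r of about 0.54 at a cut-off of 0.70, or 0.43 at 0.60; both cut-offs are assumed. For the knowledge count, internal consistency is a reasonable description but not a valid ground for changing or splitting the score. The rule suits self-efficacy.

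The consequence is a possibility: defined secondary scores could be replaced by modified versions or by single items. Whether any would be depends on baseline correlations that are not reported. The effect is confined to knowledge, attitudes, norms and self-efficacy. It is worth correcting because these scores carry four of the hypotheses and the correction is nearly free.

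**What to change.** Rewrite the paragraph so that it says the following:

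- **Knowledge** stays the fixed 0–14 count of correct answers. Alpha (KR-20) is reported descriptively and triggers no change.
- **Attitudes and norms** are exempt from factor analysis. The inter-item correlation of each pair is reported instead.
- **Self-efficacy** is the only scale open to a reliability-driven change, decided on baseline data pooled over arms and before follow-up is analysed by arm.
- **The protocol-defined score** is always reported beside any modified version.
- **Norms coding** is reconciled first, so that both items run in the direction that the score claims. This should be settled directly, not left to a discretionary reliability check.

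The cost is one paragraph of wording and less freedom to refine the scales. Reporting attitudes and norms only as four single items is another option, but it is debatable because it doubles the number of results for those two constructs; it is not needed to resolve the point.
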